## Abstract

**Background:**

Older adults represent the fastest-growing group of medical marijuana (MM) users in the United States, with chronic pain being the most common reason for use. Despite this trend, scientific evidence remains limited regarding the short- and long-term effects of MM on critical health outcomes, including cognitive function, physical and mental health, and overall quality of life, in this population. To better inform clinical practice and public policy, there is a clear need for more rigorous longitudinal studies that examine the impact of real-world MM products over time.

**Objective:**

The Study on Medical Marijuana and Its Long-Term Effects on Older Adults (SMILE) is a prospective cohort study that aims to (1) determine MM’s short- and long-term effects on pain, physical, emotional, and cognitive functioning, as well as quality of life, in older adults and (2) identify MM product characteristics and patient subgroups associated with improved outcomes and side effects.

**Methods:**

This study will recruit and follow 440 older adults (aged ≥50 years; ~50% aged >65 years, ~50% male) with chronic pain for 12 months, as some initiate MM use (MM group, n=330) and others do not (comparison group, n=110). Data collection includes quarterly survey questionnaires (longitudinal changes in cannabis use, pain, physical and emotional functioning, side effects, and quality of life); baseline and 12-month cognitive assessments, pain sensory tests, and blood and urine samples for cannabis use; and periodic smartphone- and Fitbit sensor–based measurements to capture MM use patterns, real-time pain, mental health, and objective data on physical activity and sleep. Data will be analyzed using descriptive analyses, generalized linear mixed-effects models, and generalized estimating equation models to assess differences in short- and long-term effects between the MM and comparison groups, as well as subgroups among those initiating MM treatment.

**Results:**

Recruitment for the SMILE study began in July 2022, and all data collection is expected to be completed by 2026. As of October 2025, we have enrolled 399 participants, with 277 in the MM group and 122 in the comparison group. Results are expected to be published starting in 2027.

**Conclusions:**

With multisource data collected in real time and over 12 months, our study will provide much-needed scientific evidence addressing (1) whether MM can reduce pain and improve physical and emotional functioning in the short term among older adults; (2) whether the effects of MM last for 12 months and demonstrate changes in quality of life or cognition; and (3) whether health benefits and consequences differ by MM product type and whether individual differences (eg, sex, baseline pain phenotyping) moderate the relationship. Our findings will offer valuable insights for physicians and patients when considering MM as a treatment option and will help guide more informed, individualized care decisions.

## Introduction

Medical marijuana (MM) is increasingly accessible in the United States. Its use is rising among the 36 million adults in the United States aged 45 years or older, with chronic pain accounting for 60.6% of qualifying conditions for MM use [1-4]. This increase in MM use could be attributed to state-level legalization of marijuana and older adults seeking MM as an alternative pain treatment, which reduces stigma and increases accessibility [5-7]. However, evidence on marijuana’s long-term efficacy and safety in older adults is scarce [1,8-21], as most studies only include participants under the age of 60 [22]. This is concerning, given the association of aging with polypharmacy and substantial changes in pharmacokinetics and pharmacodynamics (eg, drug clearance rate) [5,23]. Therefore, data on short- and long-term health outcomes and side effects among older adults are urgently needed [24].

While marijuana’s pharmacological profile supports a potential role in pain management, empirical evidence regarding its efficacy in treating chronic pain remains inconsistent. While some meta-analyses have reported significant beneficial effects of marijuana on chronic pain [25-27], others have found no or limited effect [28-30]. Similarly, the literature has shown that MM may help with chronic pain-related experiences—such as anxiety, depression, and opioid use—while also improving sleep and quality of life among individuals with chronic pain [31-34]. Despite the significant interpersonal differences in responses to pain treatment [35], important biological factors (eg, sex and baseline pain phenotyping), psychological factors (eg, marijuana expectancy and social desirability bias), and the use of objective measures such as sensors or biomarkers to complement self-reported outcomes [36-38] have received limited attention in marijuana and chronic pain research [22,39,40].

Research challenges—such as a reliance on the use of marijuana products not reflective of real-world usage of MM—may explain the inconsistent findings across studies [41]. While randomized controlled trials are considered the “gold standard” of evidence, the products used are often isolated or synthetic cannabinoids (eg, dronabinol) [42,43], which have limited variety and may not be comparable to MM products available in state dispensaries [32]. The ubiquitous access to MM at the state level dictates an urgent need to investigate the effects of these products, which usually have higher concentrations of tetrahydrocannabinol (THC) and/or cannabidiol (CBD) and are consumed via a greater diversity of methods (eg, vape, capsule, tincture, cream). The lack of standard guidance for MM use makes it difficult to accurately characterize the ratio of major components (THC:CBD), administration route, and dosage, all of which may influence the efficacy of MM on chronic pain [1,44,45]. There remains a critical need for systematic investigation of MM’s effects on pain, physical and emotional functioning, and overall health outcomes (eg, quality of life), as well as the need to track potential side effects, such as its impact on cognitive functioning in this population [22,46,47].

To address these critical gaps in the literature, this study will build a prospective cohort of older adults aged 50 years or older with chronic pain, including those who initiate MM use and those who do not. This study will integrate both technology-based remote assessments (eg, smartphone-based ecological momentary assessment [EMA], Fitbit sensor) and quarterly in-person visits (eg, surveys, blood tests) to systematically examine the short- and long-term impacts of MM on 6 core chronic pain outcome domains: (1) pain intensity and interference; (2) physical functioning; (3) emotional functioning; (4) cognitive function; (5) participant-rated overall improvement; and (6) adverse events or side effects [48-50], 5 of which are recommended by the Initiative on Methods, Measurement, and Pain Assessment in Clinical Trials (IMMPACT).

The specific aims of this project are as follows: (1) determine whether MM use leads to short-term changes in pain intensity and physical and emotional functioning, as measured in real time by EMA (subjective data) and the Fitbit device (objective data); (2) evaluate whether MM use leads to longer-term changes over a 12-month period, based on self-reported pain intensity or interference, emotional and physical functioning, health-related quality of life, and cellular aging markers, such as telomere length; and (3) among individuals initiating MM, examine which MM product characteristics (ie, THC:CBD ratio, administration route, dose) are associated with greater improvements in the outcomes defined in Aims 1 and 2, or with a greater incidence of side effects. Additionally, the study will explore whether individual differences (eg, sex, baseline pain phenotype) moderate these relationships.

## Methods

### Ethical Considerations

The University of Florida (UF) Institutional Review Board (IRB) approved this study (IRB202101597) on July 29, 2021, and it was conducted in accordance with the Declaration of Helsinki.

All participants will provide written informed consent prior to any study procedures being conducted, with the option to withdraw consent at any time. The study team will send participants the informed consent form remotely through a secure Research Electronic Data Capture (REDCap) link for review before their baseline visit. Participants have the option to sign the consent form remotely or after discussing study details with study staff during the baseline visit. Following informed consent, participants will complete the Rapid Estimate of Adult Literacy in Medicine, Revised to assess health literacy [51]. If participants score lower than 6 out of 8 points on the Rapid Estimate of Adult Literacy in Medicine, Revised, study staff will re-review the informed consent forms and ask follow-up questions to ensure that participants fully understand the study protocol.

Only IRB-approved study staff will have access to study information and participant data. Participants are assigned a unique study identifier to maintain confidentiality. Biospecimens are labeled with the unique study identifier, sample type, study time point, and date of collection. Whether a participant is in the MM group or the comparison group will not be disclosed to prevent bias during sample processing. All survey data will be kept in the secure REDCap system during the data collection phase. National Institutes of Health (NIH) Toolbox data will only contain the study ID as an identifier and will be emailed with encryption to the data manager for upload into REDCap. EMA data will only contain the study ID as an identifier and will be downloaded from cloud storage to a secured server at UF on a biweekly basis when active data collection is in process. Any photos of MM products (participants are instructed to avoid including any personal identifiers in the photo) uploaded by study participants during EMA surveys will be stored on a secured server. Fitbit data will be downloaded from a Fitbit database service (ie, Fitabase) via encrypted transmission. Research staff will use the unique study account to match it back to the participant’s unique study ID so the Fitbit data can be merged with other data collected from the same participant. A certificate of confidentiality was automatically granted by the NIH to protect participant privacy because the study is funded by the NIH.

Participants will be compensated for their participation, including US $60 for completing the baseline visit, US $40 for each in-person quarterly follow-up visit, and US $60 for the 12-month follow-up visit. Participants are compensated up to US $280 for EMA and Fitbit and are paid in full if they complete 80% of the EMA assessments and wear their Fitbit 80% of the time during each period. If they do not reach this threshold, prorated payments are provided. Travel compensation of an additional US $20 is provided for participants who travel 20 or more miles for the baseline and 12-month visits. Remote options for 3-, 6-, and 9-month visits are offered for individuals experiencing transportation barriers. An additional US $200 payment is provided for participants in the MM group to offset initial costs associated with beginning MM treatment if they delay initiating MM treatment for at least 3 days to provide clean baseline data (without cannabis use) for EMA and Fitbit and then obtain an MM card through the state of Florida. Participants may keep the Fitbit device as part of their compensation after the 12-month follow-up visit or return it if they do not want it. Participants are compensated or given study merchandise of equal monetary value (~US $10, eg, umbrella, mug, hand sanitizer) if they fail screening procedures after enrollment.

### Participants

#### Population

This study plans to recruit 440 older adult participants aged 50 years or older, with at least 50% over the age of 65, and with approximately 50% of the sample being male. We will try to achieve the balanced ratio by monitoring sample demographics throughout the study and adjusting recruitment techniques as needed to target necessary demographics. Among these, 330 participants will be seeking to start MM treatment during the study period, as indicated at baseline when they are enrolled in the study, and 110 participants will have no intention of starting MM treatment for at least 6 months. However, participants are free to initiate or stop MM use at any time during the study and continue participation after they join the study. If a participant decides to withdraw from the study or is lost to follow-up at any point, data will be analyzed up to the point of withdrawal.

#### Inclusion Criteria

Potential participants will be eligible for the Study on Medical Marijuana and Its Long-Term Effects on Older Adults (SMILE) if they (1) are 50 years or older; (2) have had noncancer chronic musculoskeletal or neuropathic pain [52] for 3 or more months [53], with a pain intensity level in the past week greater than zero (“0=no pain” to “10=most pain imaginable”) [54]; (3) are seeking MM treatment (for the MM group) or have no intention to start MM for at least 6 months (for the comparison group); and (4) have access to a smartphone.

Individuals aged 50 years and older were chosen due to the rising use of MM for chronic pain and the need for research on this population [5,6]. Participants must have current noncancer chronic musculoskeletal or neuropathic chronic pain, confirmed by verification of pain for 3 or more months at an intensity level greater than zero. Intention to initiate MM treatment is assessed at recruitment to determine which group enrolled participants will be in. To obtain baseline data before the initiation of MM treatment, participants must not be receiving MM treatment at the time of enrollment. Individuals who are not interested in MM should ideally not initiate MM treatment within the 6 months following enrollment. Access to a smartphone is necessary for completing the EMA and Fitbit aspects of the study. Because all assessments and questionnaires that will be used are in English, participants must be able to read English to complete study measures.

#### Exclusion Criteria

Potential participants will be excluded if they (1) are currently pregnant or nursing (by self-report); (2) self-report marijuana or CBD use in the past 30 days, or if the urine test is positive for THC; (3) report any history of using MM regularly (daily use); (4) used marijuana regularly (daily use) for over a month in the past 10 years; (5) have current or past substantial or severe substance use disorders [55], as assessed by the Drug Abuse Screening Test [56,57]; (6) are undergoing active cancer treatment, excluding certain cancers such as skin cancer; (7) have a terminal illness; (8) have neurological conditions that impact their ability to consent or complete study procedures (eg, Alzheimer disease, Parkinson disease, multiple sclerosis, head injury, stroke, and/or seizures); or (9) have active, uncontrolled psychiatric disorders (eg, schizophrenia, bipolar disorder, excluding anxiety and depression). Many of these exclusion criteria are imposed to ensure participant safety, the ability to provide consent, and the completion of study procedures.

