#### Group Assignment

Participants will be assigned to the MM group or the comparison group based on their responses to baseline screening questions regarding current interest or disinterest in starting MM treatment. Group assignment will remain consistent for each participant, regardless of whether they change their mind throughout the course of the study. Participants interested in initiating MM treatment will be given information about local MM physicians who can certify them for a Florida MM card. Additional compensation for delaying MM treatment to enroll in the study will also be provided to participants who begin MM treatment within 4 weeks after their baseline visit to cover most of the cost for MM physician visits and the initial charge to obtain their MM card in Florida.

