#### Surveys at Baseline and 3-, 6-, 9-, and 12-Month Follow-Ups

Surveys at all time points take approximately 30 to 45 minutes for participants to complete. The length of the visit can be a barrier for older adults, especially those with chronic pain. In the interest of saving participants’ time and preventing fatigue during the in-person assessment, participants will have the option to complete the survey remotely before their visit. Participants are offered snacks and beverages during in-person visits and can take as many breaks as needed. The survey includes questions such as demographics, health status measured using the Charlson Comorbidity Index and health history [67], medication and supplement use measured using the Medication Quantification Scale, patient-reported medication symptoms adapted for MM, nonpharmacological treatments [68-70], self-rated health, mental well-being, history of and current nonmedical marijuana use, and substance use. Established scales will be used to assess variables such as pain measured by the Brief Pain Inventory, Graded Chronic Pain Scale (GCPS), Patient Global Impression of Change, and Patient-Reported Outcomes Measurement Information System (PROMIS) Pain Interference Scale [71-74]; marijuana use measured by the comprehensive marijuana motives questionnaire adapted by Lankenau et al [75-78], Medical Cannabis Expectancy Questionnaire, and Cannabis Use Disorders Identification Test-Revised; substance use measured by the World Health Organization-Alcohol, Smoking and Substance Involvement Screening Test [79]; quality of life measured by the PROMIS Global-10 [80]; depression and anxiety measured by the PROMIS Anxiety and Depression Scales [81]; social desirability measured by the Marlowe-Crowne Social Desirability Scale [82]; post-traumatic stress disorder measured by the Primary Care-Post-Traumatic Stress Disorder Scale [83]; and sleep quality measured by the Pittsburgh Sleep Quality Index [84]. A full list of core survey assessments can be found in Table 2, and information on how these measures are related to each study aim is outlined in the *Analytical Strategy* section. Participants will complete the survey independently or with assistance from research staff.

**Table 2. T2:** Summary of measures included in the core and quarterly follow-up surveys.

Measure	Baseline	3, 6, and 9 months	12 month	Source
Demographics, income, and insurance	✓			N/A^a^
Medical history	✓	✓	✓	CCI^b^ and health history [67]

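### The MM initiators may include people with substantial past cannabis use, yet the stated Aim 3 models leave prior experience out and the side-effect rate pools naive and experienced starters

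*Protocol article*

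**What the plan says.** All references are to the protocol article.

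- **Label.** The Abstract (Methods) describes a cohort followed "as some initiate MM use (MM group, n=330) and others do not". The third aim, in the Introduction, is to, "among individuals initiating MM, examine which MM product characteristics" go with better outcomes or more side effects.
- **Eligibility.** Exclusion Criteria removes people who "self-report marijuana or CBD use in the past 30 days, or if the urine test is positive for THC", and people who "report any history of using MM regularly (daily use); (4) used marijuana regularly (daily use) for over a month" in the past 10 years. A current or past substantial or severe substance use disorder also excludes. Inclusion Criteria asks only that a participant is not receiving MM at enrolment.
- **Groups.** Under Group Assignment, participants are placed "based on their responses to baseline screening questions regarding current interest or disinterest in starting MM treatment", and the assignment is kept.
- **Measured history.** The survey section lists "history of and current nonmedical marijuana use". Table 2 adds, at baseline, motives for use, MM attitudes, MM expectations and a cannabis use disorder scale.
- **Side effects.** In Table 2 the marijuana-related adverse-event scale carries the footnote that restricts it to the MM group.
- **Aim 3 models.** Time-varying MM use is the exposure. The named covariates are other nonpharmaceutical pain treatments and nonmedical marijuana, both time-varying. The named moderators are gender, pain stage, marijuana expectancy and social desirability.

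**The concern.** A new-user design normally needs a rule that makes starters new to the exposure. This one ensures a recent cannabis-free interval and no history of heavy daily use, but not absence of experience. Two planned results are exposed.

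The first is Aim 3. Experienced starters may choose different THC:CBD ratios, routes or doses from naive ones, and may also respond to or tolerate them differently. Prior experience is then a common cause of predictor and outcome. A covariate for concurrent nonmedical use does not stand in for it.

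The second is side-effect incidence. With the adverse-event questionnaire given to the MM group only, the reported rate is an average over naive and experienced starters. A physician advising a patient who has never used cannabis would read it as that patient's risk. The Discussion says the findings should inform such decisions.

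**Working it through.** **1. Who can enter.** Reading the criteria together, and absent an excluded substance use disorder:

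| History | Excluded? |
|---|---|
| Any marijuana or CBD in past 30 days, or THC-positive urine | Yes |
| Daily MM at any time | Yes |
| Daily marijuana for over a month, within 10 years | Yes |
| Non-daily MM, last used 31 or more days ago | No |
| Non-daily marijuana (eg, several times a week), last used 31 or more days ago | No |
| Daily marijuana for a month or less, last used 31 or more days ago | No |
| Daily marijuana, ended more than 10 years ago | No |

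The last four rows can join either group and, if interested in MM, are placed in the MM group. The urine test and the substance-use-disorder rule do not close the gap.

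**2. The plan's own figures.** Inputs from Power and Sample Size: 0.3 SD, within-subject correlation 0.5, 3:1 ratio, 80% power, alpha 0.05 (taken as two-sided). With baseline adjustment the variance is 1 − 0.5² = 0.75. The comparison group needs (1 + 1/3) × 0.75 × (1.960 + 0.842)² / 0.3² = 87.2, so 88. The MM group is 3 × 88 = 264, total 352, and 352/0.8 = 440. This matches the plan. For Aim 3 (r = 0.3, n = 264, alpha 0.05/7, critical value 2.690), atanh(0.3) × √261 = 5.000 and power is Φ(5.000 − 2.690) = 99.0%, also matching. None of these figures is in dispute.

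**3. Aim 3: what an omitted common cause could do.** In a linear model with no direct product effect, the spurious correlation is (experience with product) × (experience with outcome). The document gives neither. If each were as large as the plan's target of 0.3, the product is 0.3 × 0.3 = 0.09. Then atanh(0.09) × √261 = 1.458, and the chance of significance is Φ(1.458 − 2.690) ≈ 11%, against a nominal 0.7%. Weaker links give less, and the sign can go either way.

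**4. Side-effect rate.** Let p be the share of experienced starters. Pooled rate = (1 − p) × naive rate + p × experienced rate. Assume 30% in naive and 15% to 25% in experienced starters:

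| p | Pooled rate |
|---|---|
| 10% | 28.5% to 29.5% |
| 30% | 25.5% to 28.5% |
| 50% | 22.5% to 27.5% |

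If experienced starters had the higher rate, the pooled figure would lie above 30% instead.

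**5. Aims 1 and 2.** If the effect in experienced starters differs from that in naive starters by g SD, the pooled MM-group effect differs from the naive one by p × g. For p of 10% to 50% and |g| of 0.1 to 0.3, that is 0.01 to 0.15 SD in absolute size. The document fixes neither p nor the sign of g.

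**6. Precision of a never-user analysis.** With the same share p removed from both groups, n = 88(1 − p) in the comparison group and three times that in the MM group. SE = √[0.75 × (1/n + 1/(3n))] = 1/√n. Power = Φ(0.3√n − 1.960).

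| p | MM vs comparison | Power |
|---|---|---|
| 0 | 264 vs 88 | 80% |
| 10% | 237.6 vs 79.2 | 76% |
| 30% | 184.8 vs 61.6 | 65% |
| 50% | 132 vs 44 | 51% |

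**The case against.** The best reply has four parts.

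First, the article never promises a cannabis-naive cohort. Initiation means starting MM treatment, and a group of mixed experience is a legitimate target population for an observational study. This stands: the criteria are not an error and need no change. The pooled estimate has to be described as what it is.

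Second, Aim 1 commits to propensity weighting, and baseline use history, attitudes and expectations are available for it. The covariate list may sit in a full protocol or analysis plan that is not shown. This also stands for Aims 1 and 2, so the absence of a list there is not part of the point. It does not answer Aim 3, where the article does name covariates and moderators. Expectancy may carry part of past experience, but it is planned as a stratifying moderator, not as an adjustment for it.

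Third, the EMA prompts also ask about symptoms such as nausea, sleepiness and dizziness, so the questionnaire is not the only tolerability record. True, but those data would equally need splitting by prior use.

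Fourth, the selection story can run either way. A reader might infer that past responders enter the MM group and past non-responders the comparison group, so that benefit is overstated and side effects understated. The document has no figure on past response. The exclusions remove recent users and anyone who ever took MM daily, so eligible former users are people who stopped, perhaps for lack of benefit. Past non-responders in the comparison group do not by themselves bias a difference-in-differences contrast, since that group supplies the untreated trend. That inference is not supported.

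**Conclusion.** The point holds in a limited form. The criteria are a 30-day washout with a bar on daily use, so the starters analysed in Aim 3 may include people with substantial earlier cannabis experience. The stated Aim 3 models neither adjust for nor stratify by it, and the marijuana-related side-effect rate blends two kinds of starter.

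The size is unknown because the share of experienced starters is not given. Under the assumptions shown, the pooled side-effect rate departs from the naive rate by 0.5 to 7.5 percentage points. An Aim 3 association with no direct product effect could reach significance about 11% of the time if both links to experience were as strong as 0.3. For the benefit contrast in Aims 1 and 2, neither direction nor size of bias can be determined. The sample-size figures are unaffected.

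**What to change.** Leave enrolment as it is; 399 of 440 were enrolled by October 2025.

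1. Before outcome results are examined by group or product, classify prior use with a written definition, for example never, past non-daily, and past daily (marijuana only, within what the criteria allow). Use the screening answers and the baseline survey. The article names nonmedical history and screening for daily MM use; the sponsor should confirm that past non-daily MM use was recorded too.
2. Include this class as a baseline covariate in the Aim 3 models and in the propensity score.
3. Report side-effect incidence by prior use beside the pooled rate.
4. For Aims 1 and 2, keep the pooled result primary and report a never-user sensitivity estimate next to it.
5. Describe the pooled estimate as the effect of starting MM treatment in a population of mixed prior cannabis experience, and add this to Limitations.

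If the item in step 1 was recorded, the cost is plan wording and one extra analysis, with no new patients or data. The price is lower precision among never-users, as tabulated in the working, which is why that estimate should accompany the pooled one and not replace it.
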